## Abstract

**Introduction:**

Hepatocellular carcinoma (HCC) is expected to become the third most common cause of cancer death worldwide by 2030. The increase in HCC is in large part due to the rising prevalence of risk factors such as type 2 diabetes mellitus (T2DM). Up to 1 in 20 people living with T2DM have liver cirrhosis, and they have a 1% to 2% incidence of HCC per year. Patients with cirrhosis enter surveillance for HCC to identify early-stage, curable tumours. A diagnosis of T2DM does not mandate testing to identify patients with cirrhosis, with testing restricted to those with additional risks. There has never been a trial and nested cost-effectiveness evaluation comparing screening all patients with T2DM for cirrhosis against usual care.

**Methods and analysis:**

The study will use a multi-centre, unblinded individual randomised controlled trial design. The aim will be to determine the effectiveness and cost-effectiveness of screening all adults with T2DM to identify those at high risk of HCC. The recruitment strategy has been supported by patient and public involvement (PPI). Participants will be identified via an automated search of primary care records and invited to participate via text. 320 participants will be randomised for screening. The screening will include measurement of bio-markers for liver fibrosis (ELF and Fib-4) and vibration-controlled transient elastography. Another 320 participants will be randomised to standard care. Demographic and medical history data will be collected at baseline from all participants. Outcome data will be collected remotely from healthcare records. The primary outcome is the proportion of participants in each arm who are referred to HCC surveillance following testing for liver disease within 12 months of randomisation. The results will be used to calculate the incremental cost-effectiveness ratio of screening via a Markov model.

**Ethics and dissemination:**

The results of this study will be presented directly to National Health Service England. Additional dissemination via conference proceedings and publication will be supported by our PPI team. Ethical approval was granted by the West of Scotland Research Ethics Service on 2 August 2023, REC reference 23/WS/0102.

**Trial registration number:**

ISRCTN17017677.

STRENGTHS AND LIMITATIONS OF THIS STUDYFirst comparison via a randomised controlled trial between risk factor-based testing for liver disease in people with type 2 diabetes mellitus (T2DM) (usual care in the United Kingdom) and screening offered to all adults with T2DM.Provides definitive cost-effectiveness of both approaches and impact on liver cancer diagnosis and survival in a real-world setting.Will delineate the relative cost-effectiveness of different non-invasive tests to identify significant liver disease in people with T2DM.Trial is limited to the United Kingdom so usual care may not be internationally representative.Short study time horizon; therefore, observation of clinical outcomes is subject to modelling rather than real-world observation.

## Introduction

 Cancer is the leading cause of mortality in patients with type 2 diabetes mellitus (T2DM)^1^ and is strongly associated with site-specific cancers including hepatocellular carcinoma (HCC).^2^ 830 200 people died from HCC in 2020, and the incidence of HCC is expected to increase by 55% in the next 20 years.^3^ HCC is now the fastest growing indication for liver transplantation,^4^ and it is expected to become the third most common cause of cancer death worldwide by 2030.^5^ HCC has a very poor prognosis with a 5-year survival of ~20%.^6^ However, if cases are identified at an early stage, curative treatments are available which include surgical resection, liver transplant or tumour ablation.^6^

A major driver for the increasing number of deaths from HCC is the increasing global prevalence of T2DM.^3 5 7^ T2DM causes liver steatosis, inflammation, fibrosis and liver cirrhosis and patients with significant liver fibrosis or cirrhosis are at risk of HCC.^8 9^ There is a high prevalence of all stages of liver disease in people living with T2DM.^10^,^14^

International guidance recommends biannual surveillance for HCC in patients with liver cirrhosis via ultrasound imaging; however, less than one-third of incident cases of HCC in patients with T2DM are identified via surveillance.^15^ Identification of HCC via surveillance is important as cancers that are identified in patients who are undergoing regular surveillance have better outcomes.^16^ To engage patients with T2DM with HCC surveillance, it is necessary to first identify patients with cirrhosis. In the past, liver disease was hard to identify because it progresses without signs or symptoms. However, several approaches have now been validated in patients with T2DM to identify asymptomatic disease. These include the utilisation of blood tests such as the Fibrosis-4 test (FIB-4)^17^ and the Enhanced Liver Fibrosis (ELF) test,^18^ as well as a simple scan of the liver which uses vibration-controlled transient elastography (VCTE) to assess the liver stiffness^1719^,^21^ as a validated marker of fibrosis.

In addition to HCC surveillance, early diagnosis of liver disease can facilitate positive interventions aimed at improving patient outcomes. These include optimisation of blood glucose control in people with T2DM, dietary modification and treatments to facilitate weight loss, moderation or complete abstinence from alcohol (a co-factor in liver disease progression for these patients^22^) and potential pharmacotherapy that reduces fibrogenesis. With respect to the latter, on 14 March 2024, Resmetirom^23^ was given conditional approval by the US Food and Drug Administration for the treatment of adults with non-cirrhotic non-alcoholic steatohepatitis with moderate to advanced liver scarring (fibrosis) alongside diet and exercise. Furthermore, selected patients could be prescribed beta-blocker therapy to reduce mortality from bleeding oesophageal varices and to reduce the risk of liver decompensation.^24^

In addition to being recommended in the USA,^25 26^ screening for liver disease in patients with T2DM and obesity has recently been adopted as a national pilot in England that has been funded by the National Health Service England (NHSE) cancer service.^27^ The national pilot uses a primary care-based search algorithm for T2DM as well as other risk factors for liver disease (such as hazardous alcohol consumption) and then invites patients into a cascade of non-invasive tests for fibrosis.

While patients with T2DM are known to have an increased risk of fibrosis and cirrhosis,^28^ there is a lack of empirical evidence supporting the implementation of this NHSE programme. Just three studies have tested a diagnostic pathway for liver disease against a contemporaneous control,^29^,^31^ and just one specifically focused on liver disease in patients with T2DM.^30^

The NHSE pilot is different from the current national (NICE) guidelines in the UK which recommend testing for liver disease is restricted to patients with risk factors for liver cirrhosis including a fatty liver on ultrasound imaging, abnormal liver enzyme levels and potentially harmful levels of alcohol consumption.^32^ T2DM alone is not a risk factor that currently mandates assessment. The reason for these narrow criteria is a lack of cost-effectiveness data supporting wider eligibility for testing.^33^

The NICE NAFLD guideline (ng49) was published in 2016,^32^ and since its publication, researchers have modelled the cost-effectiveness of testing for liver disease in patients with T2DM.^34^,^36^ Published models have compared testing strategies that include novel biomarkers and VCTE against standard care where standard care includes history, physical examination, liver ‘function’ tests (LFTs) and an ultrasound scan. The sensitivity and specificity of each approach are pre-defined and parameterise models that calculate the health gain for patients correctly categorised with liver disease and offset this against the cost of the different testing approaches by calculating an incremental cost-effectiveness ratio (ICER).^34 36^ Most recently, Forlano *et al* modelled the ICER for screening in patients with T2DM. The model was parameterised using cross-sectional data from a cohort of patients with T2DM living in London (UK) who were all tested for liver cirrhosis using FIB-4, ELF, VCTE and in 19/249 cases, liver biopsy. The costs and outcomes associated with testing this cohort were compared with usual care (primary care diagnosis) which was less accurate. In the base case analysis, the ICER was well below NICE cost-effectiveness thresholds, with the additional costs of testing being offset by the gain from an accurate early diagnosis.

However, there are challenges with extrapolating prior models to a real-world intervention such as the NHSE pilot that aims to test a broader range of adults with T2DM for liver disease as part of routine care. First, we do not know the characteristics of patients who will respond to an invitation from primary care for liver assessment. These characteristics are important—it is likely that patient age and comorbidities will influence their probability of having liver disease and their personal gain from an early diagnosis. Second, we do not know what proportion of this cohort meets clinical criteria for interventions that convey the advantage of early diagnosis, for example, what proportion enter an HCC surveillance pathway and what proportion have clinically significant portal hypertension and are started on beta blockers. Third, we do not know the real-world performance of standard care in the UK. Most patients with T2DM do not get tested for liver disease, despite their heightened risk because they are not assessed for the additional risk factors that are needed to qualify for testing. For example, LFTs are not part of an annual diabetes check-up in the UK and may or may not be measured when patients are considered for statin treatment; liver ultrasound is not a routine test, and alcohol consumption is not accurately or consistently assessed in primary care. Finally, previous economic evaluations are outdated as they use primary-care-based assessments (eg history and examination) that do not incorporate tests for fibrosis (eg Fib-4 and VCTE). Since the NICE NAFLD Guideline in 2016, tests for liver fibrosis have widely integrated into community diagnostic pathways for liver disease and therefore in future studies, models of ‘usual care’ need to reflect this.

This study protocol describes a randomised controlled trial with a nested cost-effectiveness evaluation. The study aims to compare the number of participants referred for HCC surveillance between an intervention where patients with T2DM are universally offered screening for liver disease against usual care.

## Method and analysis

The trial is described in accordance with the SPIRIT checklist.^37^ The design will be an unblinded randomised controlled trial with a nested cost-effectiveness evaluation comparing the offer of screening to *all* patients with T2DM for liver disease against standard care. We will proceed straight to an effectiveness evaluation rather than conducting a formal feasibility/pilot study. We justify this approach because the components of the intervention (used in testing for liver disease in patients with standard risk factors (eg abnormal blood results or harmful alcohol consumption)) are widely implemented. Additionally, data such as the attrition rate from the conventional diagnostic pathway is already known (see sample size section).^38^ Undertaking a randomised controlled trial in this setting is very important as this provides a contemporaneous standard care arm as a counterfactual.

### Primary outcome

The number of participants referred to secondary care with the suspected liver disease within 12 months of randomisation who are subsequently referred for HCC surveillance.

As an unblinded trial, it is important our primary outcome is as objective as possible and independent of the research team. In both study arms, patients with high liver stiffness measurements will be referred to nearby hepatology services (with thresholds defined by local practice). Via usual care, an independent local clinician will then assess the severity of liver disease. In real-world practice, this may include history, examination, no further tests or repeat VCTE, additional tests for fibrosis and in some cases liver biopsy. Regardless of the clinical approach taken, the primary outcome will be whether the clinician felt the disease was severe enough to warrant referral for HCC surveillance. Since the trial sites cover a variety of different regions across the south of England, this pragmatic approach is likely to closely reflect current UK practice.

### Secondary outcomes

The test or combination of tests for liver cirrhosis with the lowest cost per case diagnosed.*The sub-group with the lowest cost per case diagnosed.*The ICER of screening for liver cirrhosis in people with T2DM.The number of cancer deaths avoided by screening (as per Markov modelling).The number of patients diagnosed on VCTE with ≥F2 disease (defined as a liver stiffness of ≥8.2 kPa).^21^

*See (i) for the definition of a ‘case’.

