**Figure 2 F2:**
[figure not shown]
Markov model structure is used to calculate the incremental cost-effectiveness of different testing strategies. The findings from the trial will parameterise this model. Numbers 1–4 correspond to the benefits of early detection that will be incorporated into the modelling. HCC, hepatocellular carcinoma.

Our base-case analysis will closely match real-world practice. In both cohorts, patients identified with liver cirrhosis and referred for HCC surveillance will enter a separate health state—named F4_SURV. Based on recently published data, participants in this health state who develop HCC will have a higher chance of cure (ie return to their original F4 SURV health state) and a lower chance of progression to death or transplantation.^16^ Similarly, a proportion of those in F4_SURV will have a lower risk of progressing to a decompensated state that reflects the real-world number of participants who commence B blockers by recent guidelines.^45 46^ Participants identified with F2 or F3 disease will enter monitoring states (F2_Mon and F3_Mon) and undergo biannual assessment for progression to F4 disease. Monitoring will stop when participants in the model reach 80 years of age.

As part of our base case analysis, we will calculate the cost-effectiveness (cost per QALY) of four testing strategies that are broadly reflective of current testing strategies in the study region and the NHSE pilot (described in the background). These will be compared against ‘no testing’ and presented as ICERs that can then be compared between strategies.

Usual care.Reflex testing with VCTE only (ie everyone offered VCTE).FIB-4 then VCTE for patients with FIB-4>3.25.ELF then VCTE for patients with an ELF >9.5.

We will conduct probabilistic sensitivity analyses where model parameters are probabilistically varied across pre-specified distributions and ranges. The results of the probabilistic sensitivity analyses will be presented as a scatter plot and a cost-effectiveness acceptability curve.

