### Sample size

We will aim to recruit 320 patients into each arm of this study—640 patients in total (figure 3). A sample of this size will enable us to address the primary outcome, with a minimum power of 80% after allowing for a very conservative 25% drop-out rate from the diagnostic pathway in both arms. A more realistic drop-out rate would be 5% which would give the power to test the primary outcome of >90%.

We are concerned that the conduct of our study may increase liver disease diagnosed via usual care due to the Hawthorne effect on participants randomised to usual care or on primary care physicians who are more likely to request testing because they are, as a consequence of participation, more aware of liver disease.^43^ Our sample size therefore also accounts for a doubling of background liver fibrosis testing in usual care. The background testing activity for liver disease in the study setting has been very important in calculating our sample size. We have estimated the background testing activity from what we know about the number of patients tested for liver fibrosis who have T2DM in a year and the total population of people with T2DM (figure 3).

All sample size calculations were conducted using nQuery Advisor 7.0.

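### Two secondary outcomes name the test and the sub-group with the lowest average cost per case: the first puts no price on missed cases, and the second is biased low when only about 12 to 15 cases are expected

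*Protocol article*

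**What the plan says.** Under Secondary outcomes, the protocol article lists "The test or combination of tests for liver cirrhosis with the lowest cost per case diagnosed" and "The sub-group with the lowest cost per case diagnosed". Each outcome is the identity of a minimum. The definitions attach no floor on sensitivity and no comparison between strategies. A footnote sends the reader elsewhere for what counts as a case ("See (i) for the definition of a" case). The item label it points to is not visible in the text available, perhaps only because list numbering was lost. It is read here as referral to HCC surveillance after referral with suspected liver disease, as in the primary outcome.

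The Cost-effectiveness analysis section names four strategies: usual care, VCTE for everyone, and two in which a blood test decides who goes on to VCTE. One of these is "ELF then VCTE for patients with an ELF >9.5"; the other uses FIB-4 in the same way. That section also plans a lifetime Markov model giving cost per QALY, with each strategy set against no testing.

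On numbers, the Sample size section says "We will aim to recruit 320 patients into each arm of this study—640 patients in total", and the Abstract says "Up to 1 in 20 people living with T2DM have liver cirrhosis".

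**The concern.** The two outcomes fail for different reasons.

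- **Tests.** The fault is systematic. Dividing total cost by cases found rewards a strategy for not spending and charges it nothing for the cases it leaves undetected. A cheap, insensitive gate can win even though the purpose of screening is to find people at high risk of HCC.
- **Sub-groups.** The fault is selection. The lowest of several ratios, each resting on a handful of cases, tends to fall below its true value, and the sub-group that produces it may lead by chance.

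The article lists among its strengths that it will establish the relative cost-effectiveness of the non-invasive tests, and its results go directly to NHS England. A named cheapest test or best sub-group is therefore likely to be read as a finding about how to screen.

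**Working it through.** **Number of cases.** The article states no case count, so it is derived from 320 per arm, a drop-out of 5% to 25% (Sample size) and a prevalence of at most 5% (Abstract).

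- 25% drop-out: 320 × 0.75 = 240 tested; 240 × 0.05 = 12 cases.
- 5% drop-out: 320 × 0.95 = 304 tested; 304 × 0.05 = 15.2 cases.
- At an assumed prevalence of 3%: 7.2 and 9.1 cases.

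The stated power offers a rough check. The article claims "with a minimum power of 80% after allowing for a very conservative 25% drop-out rate from the diagnostic pathway in both arms", and above 90% at 5% drop-out. This cannot be reproduced strictly, because event rates and alpha are not in the text shown. Assuming 5% against 0.5% and two-sided alpha of 0.05, power is 85.6% with 240 per arm and 92.6% with 304. With 0.75% in the control arm it is 79.8% and 88.2%. The claims are compatible with about 5% in the screening arm.

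**Test outcome.** Let r = gate cost/VCTE cost, f = share passed to VCTE, and s = the share of the cases found by VCTE for all that the gated strategy also finds. Relative to VCTE for all, the gated strategy costs r + f and finds s of the cases, so

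relative cost per case = (r + f)/s,

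and the gate wins whenever r + f < s. The documents give none of these values. Assuming f = 0.10 and s = 0.5, so that 6 of 12 cases are missed:

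| r | (r + 0.10)/0.5 |
|---|---|
| 0.05 | 0.30 |
| 0.1 | 0.40 |
| 0.2 | 0.60 |
| 0.3 | 0.80 |
| 0.5 | 1.2 |

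Break-even is r = 0.5 − 0.10 = 0.40. The sensitivity a gate needs in order to win is r + f: 60% at r = 0.1 and f = 0.5, and 100% at r = 0.5 and f = 0.5.

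What the average hides can be seen at r = 0.05 with 240 people and VCTE costing 1 unit. VCTE for all costs 240 units and finds 12 cases, or 20 per case. The gate costs 0.05 × 240 + 0.10 × 240 = 36 units and finds 6, or 6 per case. The rule names the gate. The six further cases would cost (240 − 36)/(12 − 6) = 34 units each, a figure the outcome never shows.

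**Sub-group outcome.** With 12 cases in 240, the exact 95% interval for the case rate is 2.6% to 8.6%. Cost per case for the whole arm is therefore already uncertain by a factor of 0.58 to 1.92. Simulating K equal sub-groups with identical true prevalence of 5% (240 people, 200,000 runs), the lowest observed cost per case as a share of the truth is:

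| K | Median | Check: expected per group / median highest count |
|---|---|---|
| 2 | 86% | 6/7 |
| 4 | 60% | 3/5 |
| 8 | 50% | 1.5/3 |

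With four sub-groups, best and worst differ at least two-fold in 88% of runs, and in 17% at least one sub-group has no case, so its cost per case is undefined. If one sub-group truly has twice the prevalence of the others, it is picked in 88%, 65% and 50% of runs with 2, 4 and 6 sub-groups.

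**The case against.** The strongest reply is that the article already plans the right analysis. The cost-per-QALY model covers the same strategies, missed cases lose QALYs in it, and probabilistic and one-way sensitivity analyses are specified. Nothing under Secondary outcomes makes cost per case a rule for adopting a test. This stands as mitigation: a reader might infer that the trial will end up recommending an insensitive test, and the article does not support that. It does not remove the point. The model is a separate outcome, and ratios against no testing are not increments between strategies.

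A reader might also infer that the choice of test is itself mostly noise. That is not supported. The Arm 1 section gives VCTE, ELF and FIB-4 to every screening participant, so the tests are compared within the same people. In four of five assumed scenarios the strategy with the truly lowest ratio was picked in 91% to 99% of runs; only in a near-tie did this fall to 66%. For tests the rule reliably finds its minimum; the trouble is what it minimises.

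Finally, sub-group names, intervals and methods may be in an analysis plan that is not shown, and their absence from an article is no fault. Nor does the article say that sub-groups are unplanned. The point rests only on the outcome definitions: a plan that followed them faithfully would still have to name a minimum.

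**Conclusion.** The point holds, with limits, and should be acted on.

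- **Tests.** The outcome favours an insensitive gate only if the gate is cheap relative to VCTE: below 40% of its cost under the assumed 10% passed and 50% sensitivity. The real costs, pass shares and sensitivities of the FIB-4 and ELF gates are not in the document, so whether the rule will mislead here is unknown.
- **Sub-groups.** The minimum is biased low whatever the costs. The size depends on the number of sub-groups, which is not given: modest with two (median 86% of the truth) and large with four or eight (60% and 50%). With several sub-groups, chance plays a large part in which one is named.

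The count of 12 to 15 cases is a ceiling, because the prevalence is given as an upper limit. It also depends on reading a case as referral to HCC surveillance; a broader definition would give more cases and less bias.

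**What to change.** Replace the first outcome with total cost, cases found and cases missed for each strategy, together with the incremental cost per additional case across strategies ordered by cost, all with bootstrap intervals.

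Replace the second with cost per case and its interval in a few sub-groups named in advance, labelled descriptive, with no lowest sub-group declared.

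Both changes need only wording in the analysis or health-economic plan and use data the trial already collects. The price is a less simple headline.
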